#### Secondary outcomes

The secondary outcome will be patient reported health status. We will review COPD patients’ medical records to measure health outcomes such as a change in smoking status, the quantity of COPD medications prescribed, dyspnea perception and number of exacerbations in the past and over the study period.

#### Process evaluation

All aspects of the coordinated process evaluation will be implemented in this study, following the international study protocol for the TICD project, in order to identify determinants of change in chronic illness care, to examine the validity of the tailoring methods that were applied, and to analyze the association of implementation activities with the effectiveness of the program [34]. The process evaluation will comprise three main components: a structured survey with health professionals in the trials, semi-structured interviews with a purposeful sample of this study population, and standardized documentation of organizational practice characteristics. The evaluation will be guided by ‘logic models’ of the implementation programs: frameworks that specify the linkages between the strategies used, the determinants addressed by tailoring, and the anticipated outcomes.

A written survey will be undertaken involving participating health professionals. The questionnaire will list the determinants of practice, which were identified and prioritized in an earlier phase of the TICD project, respondents being asked to assess whether the program successfully targeted them. A free text field will be used to identify possible other determinants. The survey will also contain questions on the actual implementation activities that took place, to record the extent to which the target group used the offered interventions, and any adaptions made in the delivery phase of the implementation program. The core components of the implementation program will be specified. For each of the core components, content, duration, frequency and coverage will be recorded in a structured way. The content, duration, frequency and coverage aspects of intervention fidelity will also be covered. A free text field will be added to identify strategies which have been missed in the tailoring process, allowing the evaluation of the methods used for tailoring.

The face-to-face or telephone interviews will be performed with a purposive sample of health professionals. Interim analysis after five to ten interviews will be performed to adapt the interview format and purposeful sampling scheme as required.

### Data collection

At the end of the study data will be collected by review of medical records of COPD patients identified at the baseline who visited their GPs during the last nine months. Extracted information will cover the following: brief anti-smoking advice performed, information about dyspnea, COPD checklist utilization and training on using inhalers.

Patients with COPD who have given signed informed consent will be asked to fill in a questionnaire and participate in an interview containing questions about the process of care, information received from GPs and patients’ health status perception.

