**Methods/Design:**

A pragmatic two-arm cluster randomized trial has been planned to compare care following the implementation of tailored interventions of four recommendations in COPD patients against usual care. The study will involve 18 general practices (9 in the intervention group and 9 in the control group) in Poland, each with at least 80 identified (at the baseline) patients with diagnosed COPD. The nine control practices will provide usual care without any interventions. Tailored interventions to implement four recommendations will be delivered in the remaining nine practices. At follow-up after nine months, data will be collected for all 18 general practices. The primary outcome measure is physicians’ adherence to all four recommendations: brief anti-smoking advice, dyspnea assessment, care checklist utilization and demonstration to patients of correct inhaler use. This measurement will be based on data extracted from identified patients’ records. Additionally, we will survey and interview patients with chronic obstructive pulmonary disease about the process of care.

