Preliminary qualitative evidence from the authors’ earlier work showed that not one single guideline for COPD was used by all GPs or medical specialists. However, responders pointed out the individual recommendations most commonly used and the barriers to their implementation. The identified barriers for adhering to specific recommendations were: (1) lack of knowledge on smoking cessation brief intervention, (2) dyspnea evaluation tool was unavailable, (3) lack of a care plan, and (4) lack of demonstration-inhaling devices. Other research has indicated that the treatment parameters from the (COPD) guidelines are not always measured [17-19]. The consequence is that not all patients receive recommended advice and treatment from their physicians.

This study is part of the Tailored Implementation for Chronic Diseases (TICD) international collaborative research project, which is being undertaken in Germany, Norway, Poland, the Netherlands and the United Kingdom. The aim is to develop and test methods of tailoring knowledge-implementation interventions to determinants of practice in chronic illness care [20]. In Poland, the focus is on the implementation of COPD guidelines in primary care. The research group in Poland selected four key recommendations applicable to primary care (Table 1) from the four COPD guidelines most relevant to primary care and used in Poland.

**Table 1 T1:** Key recommendations for COPD management

A	Brief smoking cessation counseling is effective and every tobacco user should be offered stop-smoking advice at every contact with health care providers.
B	The prognosis of COPD should be estimated using the mMRC dyspnea scale.
C	The patient should be given the basic information about his/her disease, its treatment and the expected effects of applied drugs, in order to enhance that the patient takes an active, participating role in the long-term treatment.
D	The patient should be trained in the correct use of all devices which he/she will use for inhalation.

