### Control group

In this arm, GPs will provide their usual care for COPD patients. The practices in the control group will receive feedback after the end of the study about their own performance in comparison with the performance of other practices in the study in relation to the guideline recommendations. The GPs will receive no intervention during the study.

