### Outcomes/measures

#### Primary outcome

The primary outcome will be the GPs’ adherence to the recommendations, which is dichotomized as follows. A positive score is given if all recommendations are followed, while following less than four recommendations is given a negative score. Data listed in Table 3 will be obtained from the patients’ medical records (independent of the checklist that is provided as part of the intervention) and during interviews. All identified COPD patients who gave informed consent in each practice will be included, and full data protection procedures will be followed.

**Table 3 T3:** Information recorded in patients’ records to determine adherence of a GP the recommendations

1.	Brief anti-smoking counselling performed
2.	Dyspnea assessed
3.	Management process of COPD assessed
4.	Training patient on correct use of inhaling device performed.

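### Item 3 of the all-four primary outcome is defined incompatibly, and under the checklist-use version no control patient could meet it

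*Protocol article*

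**What the plan says.** The protocol article describes the third component of the primary outcome in four places:

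- Abstract, Methods/Design: the outcome is adherence to "brief anti-smoking advice, dyspnea assessment, care checklist utilization and demonstration to patients of correct inhaler use".
- Data collection: the items extracted from records at the end of the study are "brief anti-smoking advice performed, information about dyspnea, COPD checklist utilization and training on using inhalers".
- Primary outcome: the Table 3 data come from medical records, "independent of the checklist that is provided as part of the intervention", and also from interviews. Item 3 of Table 3 reads "Management process of COPD assessed".
- Background, Table 1, recommendation C, which item 3 is meant to reflect: "The patient should be given the basic information about his/her disease, its treatment and the expected effects of applied drugs".

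The Primary outcome section scores a patient positive only when all four recommendations are followed. The checklist is one of the tools that the implementation programme supplies (Table 2 and the COPD check list section). Of the control arm, the Control group section says: "The GPs will receive no intervention during the study".

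**The concern.** An item cannot be both use of the checklist and something assessed without reference to it. The difference matters because the checklist is handed to one arm only. A component that asks for the intervention's own form measures whether the form was supplied and filled in. It does not measure whether patients were informed about their disease. With all-or-none scoring, a component that one arm cannot meet sets the whole primary outcome to zero in that arm.

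Two other features of the plan mean that the ambiguity will not settle itself. The Blinding section says that the research assistants who assess outcomes will know the allocation, so unblinded staff would be choosing between the versions. In addition, intervention GPs are asked to write smoking advice, the dyspnea grade and inhaler training into the medical record, but for recommendation C the only recording instruction is to tick the checklist. The Primary outcome wording therefore leaves it unclear what evidence for item 3 would exist in the intervention arm once the checklist is set aside.

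**Working it through.** **1. The versions side by side**

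| Place | What makes item 3 positive | Can a control patient meet it? |
|---|---|---|
| Abstract; Data collection | Checklist used | No, if the study's checklist is meant |
| Primary outcome; Table 3 | Management process assessed, apart from the checklist | Yes |
| Table 1, recommendation C | Patient given basic information | Yes |

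**2. The composite under the checklist version**

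P(all four) = P(item 3) × P(other three, given item 3). In the control arm P(item 3) = 0, so P(all four) = 0 whatever care is given.

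**3. The plan's own sample size**

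Inputs from Sample size calculation: 40% and 60%, 80% power, two-sided alpha 0.05, ICC 0.05, 30 patients per practice.

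- Two proportions, pooled variance, no continuity correction: 97 per arm.
- Design effect: 1 + (30 − 1) × 0.05 = 2.45.
- 97 × 2.45 = 237.65 per arm; 237.65 / 30 = 7.92, rounded up to 8 practices per arm.
- Total: 16 practices and 16 × 30 = 480 patients, as stated.

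The effective size per arm is 8 × 30 / 2.45 = 98.0 with 8 practices and 9 × 30 / 2.45 = 110.2 with 9. Power for 40% against 60% is 80.4% and 84.9% respectively. The arithmetic is sound. It needs an outcome that both arms can reach, and a control rate of 0% is incompatible with 40%.

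**4. The planned model**

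Statistical methods specifies a two-level random-intercept logistic regression with odds ratios and 95% confidence intervals. With no control events the control odds are 0, the odds ratio is unbounded, and the arm coefficient has no finite maximum-likelihood value (separation). A single-level fit to an illustrative 0/270 against 108/270 (9 × 30 = 270 per arm; 108/270 = 40%) shows this. One routine stopped at a log odds ratio of about 25 with a standard error of about 13,000, another at 271,440. These are stopping points of the algorithms and not estimates.

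**5. What the contrast would measure (illustration only)**

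Assume, and neither figure is in the document, that 40% of patients in both arms truly receive all four elements of care, so there is no effect. Assume also that intervention GPs use the checklist in a share q of those patients. The checklist version then compares 0% with 0.40 × q: 10%, 20%, 30% or 40% for q = 0.25, 0.5, 0.75 or 1. The whole difference comes from the form.

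**The case against.** The strongest reply is that the section headed Primary outcome should govern. It sets the intervention's checklist aside, Table 3 mentions no checklist, and interviews are named as a source that control patients can supply. The Data collection list says what will be extracted and does not say how it is scored. Only the abstract ties checklist use to the outcome directly. This stands to the extent that 0% is a conditional result. It needs the abstract and Data collection to be followed, and it needs the checklist to be the study's own. That is the only one described, but a control practice with its own checklist is not addressed. The independence clause also covers all the Table 3 data and not item 3 alone, though item 3 is where it collides with the other sections.

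A reader might infer more: that the trial is decided by construction, and that a handful of intervention patients against none would be declared a success. For example, 6 against 0 at an effective 110 per arm gives a Fisher p of 0.029. The document does not support this. Fisher's test is not planned, and those counts are deflated by the design effect and are not patients. Under the planned model a Wald test of the separated fit in step 4 gives z of about 25/13,000 = 0.002, far from significance. A likelihood-ratio test would behave differently, and the article does not say which is used. Separation makes the planned estimate unusable; it is not shown to guarantee a positive result.

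A reader might also say that the checklist version contradicts a stated control rate of 40%. The sample size text does not call 40% the control rate of the all-four composite. That reading is inferred because it reproduces the 16 practices.

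**Conclusion.** The contradiction is real and concerns the primary outcome. Four passages give three incompatible versions of item 3, and they must be reconciled. This is not condensation by the journal, because the article states the item repeatedly and differently.

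The size depends on which passage the extractors follow. Under the abstract and Data collection, with the checklist meaning the study's own, three things follow: a control composite of 0% by definition, no finite odds ratio from the planned model, and planning rates of 40% and 60% that cannot apply to the composite. Under the Primary outcome section the control arm is not fixed at zero, and the fault shrinks to two misworded sections plus an unsettled rule for the checklist tick. The sample size arithmetic is not in question. Because extraction happens at the end of the study, the point can still be settled beforehand and should be.

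**What to change.** By dated amendment, before any record is extracted:

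1. Define item 3 once, as documented delivery of the information in recommendation C (the disease, its treatment and the expected drug effects). Score it by the same rule in both arms from the sources named under Primary outcome, namely records and interviews. Table 3 must be reworded too, because its present text is not recommendation C.
2. State how a tick on the study checklist is handled. The form should be neither required for a positive score nor the sole evidence for one.
3. Bring the abstract, Primary outcome with Table 3, and Data collection into line with that definition.
4. Keep checklist use as a separate variable outside the score, reported only for the intervention arm as a fidelity measure. The professional survey in the process evaluation already asks how far the offered interventions were used.

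The cost is an amendment and a revised extraction form. Practices are already randomised and interventions delivered, so the date of the amendment relative to extraction must be on record. One downside is that the intervention-arm rate on item 3 may fall, because GPs there were told to document recommendation C only by ticking the checklist.

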### Statistical methods

The primary analysis will be on an intention to treat basis. Missing values will be inputted with a multiple imputation method. Data will be coded, cleaned and locked before any analyses are made. Quantitative data will be analyzed in aggregate, using the Statistical Package for the Social Sciences (SPSS, (version 17, IBM Corp.) and Statistica (v10, StatSoft Inc.). Study groups will be compared with respect to the determinants of COPD and its improvement. Only members of the research team who need access to the database to fulfill their roles within the study will be granted access to the database. Demographic characteristics of the practices and the participants within the practices will be described using percentages, measures of central tendency (means or medians) and measures of variation (standard deviations or ranges). The analysis will be based on the patients nested within practices two-level model. The primary endpoint is the GPs adherence to four COPD guidelines after nine months, in each practice. Secondary endpoints are the change in smoking status and health care utilization during the nine months amongst included patients. Data will be compared between arms using logistic regression (with logit link function and binomial distribution) with patient at level one and practice at level two. The ICC and odds ratios and 95% confidence intervals will be estimated using two-level random intercepts logistic regression models. The significance level will be set at α = 0.05 for all analyses.

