### Randomization

Randomization will be performed by a statistician not involved in the trial, through a computer. The general practices will be allocated randomly to two equally sized groups: an intervention group and a control group. At the end of the study a group of patients will be randomly selected in order to invite them to fill out the end-of-study questionnaire. Participants in this trial will not be blinded. Descriptive statistics and logistic regression will be used for analyzing the data. The level of statistical significance will be *p* < 0.05.

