#### Dyspnea evaluation

Second, an additional form containing the modified Medical Research Council Dyspnea Scale (mMRC) will be inserted into patients’ medical records on paper. It is a validated patient symptom questionnaire for a subjective assessment of COPD symptoms. This intervention will address the recommendation of National Institute for Health and Care Excellence based on Fletcher et al. [31].

GPs will be asked to determine the patient’s status according to the scale and put this information into the patient’s medical records.

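### The secondary outcomes differ between two sections, and the only between-arm model, a binomial logistic regression, does not suit the counts and amounts among them

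*Protocol article*

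**What the plan says.** The protocol article defines the secondary outcomes in two places.

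- **Secondary outcomes section:** "The secondary outcome will be patient reported health status". It then plans a review of medical records for further measures, listed as follows: "a change in smoking status, the quantity of COPD medications prescribed, dyspnea perception and number of exacerbations in the past and over the study period".
- **Statistical methods section:** "Secondary endpoints are the change in smoking status and health care utilization during the nine months amongst included patients".

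On the model, the next sentence of Statistical methods is general: "Data will be compared between arms using logistic regression (with logit link function and binomial distribution"), with patients at level one and practices at level two. The Randomization section adds: "Descriptive statistics and logistic regression will be used for analyzing the data". No other between-arm method is named. The Primary outcome section says how adherence is made binary. No such rule is given for any secondary outcome.

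On data sources, the Dyspnea evaluation section, part of the implementation program, provides for "an additional form containing the modified Medical Research Council Dyspnea Scale (mMRC") to be placed in patients' paper records and asks GPs to record the result. The section on smoker identification gives intervention GPs training and asks them to record what they do. The Control group section says that control GPs get no intervention during the study. The Data collection section plans a patient questionnaire and interview that cover perceived health status, with no restriction by arm.

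**The concern.** Three things are at stake, all for the secondary results.

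1. **Which outcomes are prespecified.** With two lists, either could be reported as the planned one. The outcome that one section presents as the secondary outcome is absent from the other, and utilization appears only in the other.
2. **How they are analyzed.** Followed literally, the text sends counts and amounts through a binary model. That needs cut-offs, and cut-offs chosen after the data are seen undermine prespecification. Splitting a count at a threshold also discards information.
3. **Whether chart-based dyspnea and smoking are comparable.** The intervention aims to change what GPs write down. A difference between arms in recorded dyspnea or smoking could therefore partly reflect recording rather than how patients fared.

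**Working it through.** The plan gives no figure for the secondary outcomes, so the check is a side-by-side reading.

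**Step 1. Compare the lists and the data types.** The types are inferred from the names of the outcomes, because the article does not define scales.

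| Outcome | Secondary outcomes section | Statistical methods section | Likely type | Binomial model usable without a new cut-off? |
|---|---|---|---|---|
| Health status (patient report) | yes | no | score | probably not |
| Smoking change | yes | yes | binary, if defined so | yes |
| Medication quantity | yes | no | amount or count | no |
| Dyspnea perception | yes | no | ordinal grade | probably not |
| Exacerbations | yes | no | count | no |
| Health care utilization | no | yes | not defined, probably count | probably not |

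The first list has 5 outcomes and the second has 2. They share 1, so there are 5 + 2 − 1 = 6 distinct outcomes, and 5 of the 6 stand in one list only.

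**Step 2. Could one list be shorthand for the other?** Utilization might be meant to cover prescriptions or exacerbations, but the text does not say so. It cannot cover health status or dyspnea. The Data collection section does not settle the matter: its list of items taken from records includes dyspnea but not smoking status, medications, exacerbations or utilization.

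**Step 3. Check the scope of the model.** The logistic regression sentence follows directly on the secondary endpoints and refers to the data in general. The Randomization section repeats logistic regression and adds only descriptive statistics. From the last column of the table, the model suits 1 of the 6 outcomes as it stands, clearly does not suit 2, and probably does not suit the other 3.

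**Step 4. Check the recording by arm.** Only intervention practices receive the dyspnea form and the smoking training, each with a request to record. The Background section lists the lack of a dyspnea evaluation tool among the barriers found beforehand, and Table 3 makes assessed dyspnea a component of the primary outcome. If the intervention works, dyspnea will be recorded more often in that arm. The safeguard in the Primary outcome section, that data are independent of the checklist, names the checklist only and concerns the primary outcome. The article gives no recording rates, so no size can be calculated.

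**Step 5. Size of the questionnaire data.** The Sample size calculation section assumes 58% response and 35% dropout from 80 patients per practice: 80 × 0.58 × (1 − 0.35) = 80 × 0.58 × 0.65 = 30.16. On the plan's own assumptions, about 30 patients per practice, or 18 × 30.16 ≈ 543 in all, would supply questionnaire items.

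**The case against.** The strongest reply is that this is a condensed article. Models for single secondary outcomes are commonly left to a full analysis plan, and the logistic model plainly suits the binary primary outcome. Nothing says that counts will be dichotomized, and utilization is undefined, so calling it a count is an assumption. This stands in part: silence on models would be no finding. But the text is not silent. It assigns one model to the data without restriction, and the contradiction between the lists does not depend on any unseen document.

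On dyspnea, a reader might go further and infer that it is read from the mMRC form, that control values for dyspnea and smoking are therefore missing by design, and that multiple imputation would fill them mainly from intervention data. The documents do not support this. The stated source is the medical record, and control GPs may note dyspnea and smoking in usual care. The imputation sentence follows the one on the primary analysis and names no variables, model or handling of arms. What remains is that recording will probably differ by arm and that no common source or scale is stated.

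A further objection concerns the remedy. Patients are approached only at follow-up, so a question on current smoking cannot by itself give a change. Questionnaire items bring non-response, in a trial whose participants are not blinded. Both points stand and limit what the questionnaire can do. Health status already comes from patients, so it needs no new source.

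**Conclusion.** The point holds for the lists and the model, and in a limited form for recording.

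- **Lists:** a direct contradiction. One of six outcomes is common to both sections.
- **Model:** the one stated model does not fit exacerbations or medication quantity without unstated cut-offs. That it also fails for utilization, health status and dyspnea is probable but rests on assumed scales. That it fits smoking change assumes a binary definition.
- **Recording:** a probable difference between arms in charted dyspnea and smoking, of unknown size. It is an inference from who is given the tools and asked to record, not something that the article states.

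The primary outcome and the sample size are not affected. The changes should be made, but the weakness does not threaten the main result.

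**What to change.** 1. Use one list of secondary outcomes, word for word, in the Secondary outcomes and Statistical methods sections. Define utilization, or drop it, and bring the Data collection items into line.
2. Limit the two-level logistic model to binary outcomes: adherence and smoking change.
3. Analyze exacerbations and other counts with a negative-binomial or Poisson model with a practice random intercept. Adjust exacerbations for the past count that the Secondary outcomes section plans to collect, and state the period that it covers, which is now open.
4. Use a linear or ordinal mixed model for health status, according to the instrument.
5. Take dyspnea, and current smoking as a supporting measure, from the end-of-study patient questionnaire, asked identically in both arms.

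**Cost:** protocol wording, at most two questionnaire items, and a check that the named software can fit mixed count models. The Trial status section says that the interventions have been delivered, so the change should precede follow-up data collection, or at least any look at the data by arm. The downside is that the questionnaire items exist only for responders, about 30 per practice on the plan's assumptions, and that smoking change still needs a baseline value from records or recall.

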### Eligibility criteria

#### Patients

Eligible patients will be approached at follow-up. Only patients who were treated in the same practice at baseline (with the labelled medical records) will be considered for inclusion so that the study is prospective. Exclusion criteria are: (1) terminal illness and (2) cognitive impairments. At follow up 80 patients, randomly selected (with personal data unknown to researchers) will receive an informed consent form and an invitational letter via their GPs, and will be asked to fill in a questionnaire and/or participate in an audio taped interview or focus group. This letter will provide comprehensive information about the study. Contact details of the researchers will be provided so that patients can ask questions. Patients’ information gathered from questionnaires or from interviews will be anonymized.

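### Record review is limited to patients who saw their GP in the nine months, yet health care utilization is compared over those same months in a patient set that other sections define without a visit condition

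*Protocol article*

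**What the plan says.** The endpoint is named in one place only, Statistical methods: "Secondary endpoints are the change in smoking status and health care utilization during the nine months amongst included patients". The term is not defined. Secondary outcomes does not list it; that section names patient-reported health status, smoking status, quantity of COPD medication, dyspnea and exacerbations.

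The protocol article describes the patients who supply data in four ways:

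- Data collection: end-of-study "review of medical records of COPD patients identified at the baseline who visited their GPs during the last nine months".
- Eligibility criteria, Patients: "Only patients who were treated in the same practice at baseline (with the labelled medical records) will be considered for inclusion". No visit during follow-up is required.
- Primary outcome: "All identified COPD patients who gave informed consent in each practice will be included". Again there is no visit condition.
- Secondary outcomes: "We will review COPD patients’ medical records to measure health outcomes such as a change in smoking status". No visit condition is stated here either.

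The follow-up window in the Abstract is the one used in the visit rule: "At follow-up after nine months, data will be collected for all 18 general practices". For analysis, Statistical methods states "The primary analysis will be on an intention to treat basis", which speaks only of the primary analysis, and describes the model in general terms: "Data will be compared between arms using logistic regression (with logit link function and binomial distribution", with patients nested in practices.

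**The concern.** Seeing the GP during the nine months happens after practices are randomized. It is also part of what health care utilization would normally measure. If records are extracted only for patients with a visit, a labelled patient who made no GP visit leaves the data because of that zero. The arms are then compared per attender rather than per labelled patient, and the attenders in the two arms need not be comparable.

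Requiring a visit can be defended when the question is what the GP did at visits, as for the adherence outcome. That defence does not carry over to an endpoint that counts use of care. What is at stake is a secondary endpoint whose between-arm difference could be distorted, and whose denominator two readers of the article could set differently.

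**Working it through.** **1. Figures in the plan.** None is given for utilization. The stated sample size concerns adherence and reproduces:

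- Two proportions, 0.40 against 0.60, two-sided alpha 0.05, 80% power, pooled formula: 97 per arm.
- Design effect 1 + (30 − 1) × 0.05 = 2.45, so 97 × 2.45 = 237.65 per arm. Dividing by 30 gives 7.92, hence 8 practices per arm and 480 patients.
- Baseline patients per practice: 30 / (0.58 × 0.65) = 79.6, hence 80.

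Nothing below changes these.

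**2. The sections side by side.**

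| Section | Visit in the nine months required? |
|---|---|
| Eligibility criteria, Patients | No |
| Primary outcome | No |
| Secondary outcomes | No |
| Data collection | Yes |
| Statistical methods | Says only that patients are included |

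Data collection is the only section that sets whose records are pulled at the end of the study. The questionnaire and interview cover process of care, information received and perceived health, so no other stated source supplies utilization for patients without a visit.

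**3. Uniform shift (assumed rates).** For a Poisson count with mean m, the mean among those with at least one visit is m / (1 − e^(−m)).

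| Control mean | Intervention mean | True difference | Visitors only | Difference in visitors |
|---|---|---|---|---|
| 1.0 | 1.5 | 0.50 | 1.58 vs 1.93 | 0.35 |
| 2.0 | 2.5 | 0.50 | 2.31 vs 2.72 | 0.41 |
| 3.0 | 3.5 | 0.50 | 3.16 vs 3.61 | 0.45 |

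The control share with no visit, e^(−m), is 37%, 14% and 5% in the three rows. The difference shrinks by about 30%, 18% and 10%. It does not change sign.

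**4. Low users brought in (assumed rates).** Suppose a share s of control patients make no visit and the rest average 4. In the intervention arm, half of the non-attenders come once.

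- All labelled patients: control 4(1 − s); intervention 4(1 − s) + 0.5s.
- Visitors only: control 4; intervention [4(1 − s) + 0.5s] / (1 − 0.5s).

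| s | All labelled | Difference | Visitors only | Difference |
|---|---|---|---|---|
| 30% | 2.80 vs 2.95 | +0.15 | 4.00 vs 3.47 | −0.53 |
| 15% | 3.40 vs 3.475 | +0.075 | 4.00 vs 3.76 | −0.24 |
| 5% | 3.80 vs 3.825 | +0.025 | 4.00 vs 3.92 | −0.08 |

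Here the sign reverses, because the newcomers are all low users.

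**5. The logistic model.** If the endpoint were any GP visit, the proportion among included patients would be 100% in both arms by construction. No odds ratio can be estimated.

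**6. Other components.** Hospital use, for example, would be conditioned on GP attendance and not on its own value. The condition is still a post-randomization event.

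**The case against.** The best defence is that the visit rule may not apply to this endpoint. In Data collection, the rule is followed by a list of what is extracted, and that list is the four adherence items; utilization is not on it. Secondary outcomes describes record review without restriction, and the eligibility and primary outcome sections carry no visit condition. This stands in part. It shows that the sections disagree, and it rules out treating the restriction as certain. It does not remove the restriction from the only rule for end-of-study extraction.

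It is also fair that utilization is undefined and may not mean GP visits. An article may leave that definition to a fuller document, and its absence is not the point here.

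A reader might infer that the endpoint is certainly measured only in users of care and will point the wrong way. The article does not support that. The program works inside consultations through GP training, a dyspnea form, a checklist and demonstration inhalers. No recall or outreach is described, and the Discussion says the trial targets GPs. Record labelling appears among the interventions in Table 2, but the sample size and participant sections describe it as the way patients are identified, without limiting it to one arm. An effect on attendance is possible, since the checklist aims at more active patients, but it is not well supported. Nor can the 35% dropout in the sample size section be read as a non-attendance rate.

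**Conclusion.** The concern holds as a conflict between sections with a real consequence if the Data collection rule is followed as written. The utilization comparison would then be conditioned on attendance after randomization and, for any GP-visit component, on the outcome itself.

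The size is not known, because the article gives no visit rates. Under the assumed Poisson shift, a true difference of 0.50 visits becomes 0.35 to 0.45. Reversal requires that the program change who attends, and with few non-attenders the figures are small (+0.025 against −0.08 at 5%). If the program left attendance unchanged, the attenders would remain comparable, and the result would simply be per attender rather than per patient. The failure of a logistic model for any GP visit needs no assumed rates; it follows from the selection rule once the endpoint is defined that way.

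This is a secondary endpoint. The primary outcome and the sample size are not affected by this point.

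**What to change.** Reconcile the sections with a statement that covers the following:

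- **Set:** health care utilization is analysed in all patients labelled at baseline who meet the criteria under Eligibility criteria and the plan's consent rule, whether or not they visited the GP.
- **Zeros:** patients still registered with no visit count as zero GP visits. They are observed zeros, not missing values to be imputed.
- **Deaths and departures:** handled by time at risk or as missing, not as zero.
- **Model:** a practice random effect with a distribution suited to the defined measure, for example a count model if the measure is a number of visits.

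Any visit requirement kept for the adherence items should be stated as applying to those items only.

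The cost is slightly more extraction work: zero visits, deaths and departures must be logged. The labelled charts have to be checked anyway to find out who visited. The change does not remove selection through consent, which the plan seeks at follow-up; it removes only the visit condition.
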